#### Cervical isometric maximal strength

Next, the cervical strength tests will be performed seated too, using a manual dynamometer (Micro FET2, Hoggan, Salt Lake City, USA). To obtain the maximum isometric force of the neck muscles in the 6 movements, a "make test" will be performed: the experimenter will resist the subject's force without trying to exceed it. The subject will be asked to perform progressively and as hard as possible, from the neutral position, a flexion movement (resistance applied under the chin), an extension movement (resistance applied to the back of the occiput), a right and left rotation movement (resistance applied along the horizontal side of the right and left mandibles), and a right and left tilt movement (resistance applied above the right and left ears).

#### Quadriceps strength

The same type of test will be performed to measure the maximal isometric extension force of the dominant quadriceps by applying the dynamometer to the lower tibia and requesting leg extension from a 90° flexion position [59].

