### Participants

#### Inclusion criteria

Volunteers for the study will be included if they are 65 years of age or older, of either sex, autonomous, able to walk ten meters alone without walking aid and able to understand instructions necessary for the correct performance of the measurements.

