#### Recruitment

Participants will be recruited from the local population by announcement. The study will be advertised on posters displayed at town halls, senior gyms, senior associations, pharmacies. Those who apply will be referred to a therapist who will make sure all eligibility criteria are met and give more information.

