#### Intervention

The experiment will take place over three measurement times on Day 0 (D0), D7 and D21. On D0 subjects will be randomized in 2 groups: experimental and placebo group. Both groups will be assessed on: SPPB, WS, lower limb strength, balance, HRV and cervical spine strength and mobility. They will also be given an SF 36 questionnaire (to complete at home and bring back to D7). Then the experimental group will receive a MFR protocol applied to the cervical spine and the placebo group will receive a placebo light touch protocol. The intervention will be followed by the same measurements as before. This schedule will be reproduced on D7. On D21, only assessment will be done. Measurements will be made by the same experimenter for all sessions for the same patient. The time of presence required is estimated at 4 h maximum: approximately 1h30 on D0 and D7 and 45 min on D21.

The MFR protocol applied to the cervical spine in this study is carried out by one therapist—Osteopath D.O. (Diploma in Osteopathy)- with one year of experience. All the gestures performed and described below are manual osteopathic techniques with myofascial aim, mastered and commonly used in osteopathic practice management. Whatever the patient's allocation group, the techniques are gentle and progressive, the patient's head (lying on his back) remaining in line with the spine.

For the treated group, initially, the manual therapist, seated at the head of the patient, will perform a “suboccipital decompression” [46]—Fig. 2a. To do this, he will position the last 4 fingers of each hand towards the lower part of the occiput, the last phalanges in contact with the sub-occipital muscles. He will look for a so-called “bone contact” on the occiput. He will apply anterior and superior continuous pressure during 15 to 20 chest breaths.

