### Secondary outcome

The secondary outcomes will be as follows: HRV, cervical range of motion, cervical muscle strength, quadriceps strength, static posturography and plantar support.

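### Maximal knee extension is tested against the experimenter's own hand resistance, so any participant who can out-push the experimenter is recorded at about the experimenter's limit; how many are affected is unknown, and an anchored strap would remove the problem cheaply.

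*Protocol article*

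**What the plan says.** All references are to the protocol article.

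- **Device and resistance.** Under Cervical isometric maximal strength, neck force is measured "using a manual dynamometer (Micro FET2, Hoggan, Salt Lake City, USA") in a make test: "the experimenter will resist the subject's force without trying to exceed it".
- **Carry-over to the leg.** The section headed Quadriceps strength then reads: "The same type of test will be performed to measure the maximal isometric extension force of the dominant quadriceps by applying the dynamometer to the" (the site named is the lower tibia). The knee position is fixed by "requesting leg extension from a 90° flexion position". A method source is cited. The text mentions no strap, frame or anchor, and no rule for a trial in which the experimenter gives way.
- **Role of the measure.** Quadriceps strength is one of the secondary outcomes: "HRV, cervical range of motion, cervical muscle strength, quadriceps strength, static posturography and plantar support". It is the only direct measure of lower-limb force; the SPPB is a functional score.
- **Who is tested, and by whom.** Participants are "autonomous, able to walk ten meters alone without walking aid", aged 65 or older. On recruitment: "The study will be advertised on posters displayed at town halls, senior gyms, senior associations, pharmacies". Under Intervention: "Measurements will be made by the same experimenter for all sessions for the same patient".

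**The concern.** The outcome is described as a maximal isometric force. With hand resistance it is both maximal and isometric only while the experimenter can hold the leg still. Beyond that the leg moves, and the dynamometer shows roughly what the experimenter could hold. The neck procedure is thus carried over unchanged to a stronger movement.

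Because the same experimenter tests a given patient at every session, the same limit applies before and after treatment. There are three cases:

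- A participant who stays below the limit is measured correctly.
- A participant who crosses the limit after treatment has the gain cut short.
- A participant already at the limit at baseline can show no gain.

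The stake is a between-arm difference in quadriceps strength pulled towards zero. A null result on this outcome could then be read as no effect when the measurement could not have shown one. The planned exploration of links between parameters would also use capped values. Unless the affected trials are marked when they happen, they cannot later be told apart from true maxima.

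**Working it through.** **The plan's own figure.** None is given for quadriceps strength. The only sample-size figure is 20 per group, for walking speed (difference 0.2 m/s, SD 0.2, power 90%, alpha 0.05, dropout 10%). It reproduces with a one-sided alpha: n = 2 × (1.645 + 1.282)² × (0.2/0.2)² = 17.1, rounded up to 18, and 18/0.9 = 20. The present point does not depend on it, except that 18 evaluable per arm is used for power below.

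**Inputs for the illustration, all assumed.** Knee-extension force is normal with SD 90 N, mean 300 N in the sham arm and 345 N in the treated arm. The true gain is therefore 45 N, and the true d is 45/90 = 0.50. One limit L applies to everyone, varied from 250 to 500 N. The recorded value is min(true force, L).

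**Formulas.** With a = (L − μ)/σ:

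- share capped = 1 − Φ(a)
- recorded mean = μΦ(a) − σφ(a) + L[1 − Φ(a)]
- recorded mean square = (μ² + σ²)Φ(a) − σ(μ + L)φ(a) + L²[1 − Φ(a)], which gives the recorded SD
- recorded d = difference in recorded means / √[(SD₁² + SD₂²)/2]

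**Worked case, L = 350 N.**

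- Sham: a = 50/90 = 0.556, Φ = 0.7107, φ = 0.3419. Mean = 300 × 0.7107 − 90 × 0.3419 + 350 × 0.2893 = 283.7 N.
- Treated: a = 5/90 = 0.056, Φ = 0.5222, φ = 0.3983. Mean = 345 × 0.5222 − 90 × 0.3983 + 350 × 0.4778 = 311.5 N.
- Difference: 27.8 N, and 27.8/45 = 62% of the truth.
- Recorded SDs are 68.4 and 54.2 N, pooled 61.7 N, so d = 27.8/61.7 = 0.45.

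**Full range.** Power is for a two-sided t-test at 0.05 with 18 per arm, by simulation.

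| Limit (N) | Sham values capped | Recorded difference (N) | Share of true 45 N | Recorded d | Power |
|---|---|---|---|---|---|
| 250 | 71% | 9.6 | 21% | 0.32 | 13% |
| 300 | 50% | 18.1 | 40% | 0.40 | 21% |
| 350 | 29% | 27.8 | 62% | 0.45 | 26% |
| 400 | 13% | 36.1 | 80% | 0.48 | 29% |
| 450 | 4.8% | 41.4 | 92% | 0.50 | 31% |
| 500 | 1.3% | 43.9 | 97.5% | 0.50 | 31% |
| none | 0% | 45.0 | 100% | 0.50 | 31% |

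The difference in newtons shrinks faster than d because capping also narrows the SD. The article says that Cohen's d will be reported for all outcomes, so both columns matter.

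**The case against.** The strongest reply is that the decisive premise is not in the document. Nothing states how strong the participants are or what the experimenter can hold. That knee extension is stronger than neck movement does not show that it exceeds the experimenter's capacity in people aged 65 or older. This stands: the size of the problem is unknown, and the range must include benign cases. In the table, limits of 450 N and above cost almost nothing, and at 350 to 400 N d falls only to 0.45 to 0.48. Placing the device on the lower tibia also helps, because the longer lever arm lowers the force to be held for a given knee torque.

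A second reply is that the article is condensed and cites a source for the method, which may use a fixed or belted device. This stands in part. The missing mention of a strap alone proves nothing. But the text does state a method: it refers back to a test in which the experimenter resists. If the device is in fact anchored, the sentence should say so.

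A reader might be tempted by three stronger readings that the article does not support:

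- **That the outcome cannot show a gain.** A gain is lost only for participants at the limit and cut short for those who cross it.
- **That this sample is especially strong.** Senior gyms are one of four kinds of poster site, and eligibility asks only for autonomy and an unaided ten-metre walk.
- **That different experimenters bias the comparison.** Data collection mentions evaluators in the plural, but Randomization and blinding refers to a single evaluator. With random allocation and a blinded evaluator, differences in experimenter strength are noise with respect to arm, not bias.

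**Conclusion.** The point holds as a design improvement. The quadriceps method as written puts a ceiling on the reading at whatever the experimenter can hold, and the plan neither removes nor records it. Under the assumed force distribution the loss runs from severe (21% of the true difference, d = 0.32, limit 250 N) to negligible (97.5%, d = 0.50, limit 500 N). The document does not allow a choice within that range.

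The distortion is towards no difference, so it would not manufacture a benefit. It affects one secondary outcome and leaves the primary outcomes and the sample size untouched. It deserves action because it is cheap to prevent and cannot be repaired after the data are in.

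**What to change.** Under Quadriceps strength, state that the same dynamometer is held at the lower tibia by a non-stretch strap anchored to the chair or table, so that the strap and not the experimenter resists the extension. Keep the 90° position and the make-test instruction. If the device is already anchored, one sentence saying so settles the point.

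If the test stays hand-resisted, record every trial in which the leg moves or the experimenter gives way, and treat those values as lower bounds (right-censored) in the analysis.

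Cost: a strap, a little set-up time at each measurement and a sentence of text; no extra staff or visit. The downside is that values become less comparable with hand-held norms, which the between-arm comparison does not need.

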#### WS, SPPB test and plantar support

The subject will then be asked to stand up and perform the different steps of the SPPB test following the instructions of the evaluator [60, 61], leading to an overall score out of 12 points. He will perform the 4 m gait measurement part (which will measure WS) equipped with W-INSHOE plantar sensors (Medicapteur, Balam, France). Data will be analyzed using the software of the same name. The sensors are attached to the skin with hypoallergenic tape.

#### Static posturography test

Finally, the static posturography test will be performed under standard conditions using the WIN-POSTURO platform (Medicapteur, Balma, France) allowing the measurement of displacements of the CoP in a static standing position at a frequency of 40 Hz for 25.6 s [62]. The measurement will be repeated 3 times. The data collected will be processed using WIN-POSTURO software (Medicapteur, Balma, France).

### Statistical analysis and sample size

We calculated 20 subjects per group would allow statistical power of 90% to detect a clinically meaningful increase in WS of 0.2 m/s (± 0.2) with an alpha risk of 0.05 and considering a dropout probability of 10%. SPPB score was not used to calculate the sample size because of the ceiling effect reported for individuals who have high functional abilities, although it remains relevant as primary outcome combined with WS [63].

All data will be expressed as mean ± SD. Normality will be verified by an Agostino-Pearson test. Comparison of data between the two groups will be performed with a one-way ANOVA, followed by a Tukey post-hoc test or a Kruskal–Wallis test, and finally by a Dunn post-hoc test. The gender effect will be considered with a two-way ANOVA, followed by a Bonferroni post-hoc test. The significance level was set at p ≤ 0.05. The effect size of Cohen’s *d* will be calculated for all outcomes and classified with 0.20, 0.50 and 0.80 thresholds to interpret small, medium or large effect. Statistical analyses will be performed using GraphPad Prism 6 (GraphPad Software, La Jolla, CA, USA).

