### Primary and secondary objectives

The primary objective of this work will be to evaluate the influence of some MFR techniques address to cervical spine on WS and SPPB (Short Physical Performance Battery test) score. It can be assessed by the main hypothesis:

H0: SPPB score and WS of MFR protocol group ≤ SPPB score and WS of light touch group.

H1: SPPB score and WS of MFR protocol group > SPPB score and WS of light touch group.

Secondary objectives will be to evaluate the influence of the protocol on other measured balance parameters, including cervical strength and mobility as well as lower limb strength, ground support and HRV. The data can also be used to explore the relationships between the different parameters.

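### The stated 90% power with 20 per group fits a one-sided 5% test, but the planned ANOVA is two-sided and gives about 83% for walking speed

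*Protocol article*

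**What the plan says.** Three statements in the protocol article bear on this point.

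- **Hypotheses** (Primary and secondary objectives). The alternative is directional: "H1: SPPB score and WS of MFR protocol group > SPPB score and WS of light touch group". The null is the complementary ≤ statement.
- **Sample size** (Statistical analysis and sample size, first paragraph). "We calculated 20 subjects per group would allow statistical power of 90% to detect a clinically meaningful increase in WS". The effect to be detected is put at 0.2 m/s (± 0.2), alpha at 0.05 and the dropout probability at 10%. Sidedness is not given.
- **Analysis** (same section, second paragraph). "Comparison of data between the two groups will be performed with a one-way ANOVA", with Kruskal–Wallis as the non-parametric alternative, and "The significance level was set at p ≤ 0.05". No one-sided use of either test is described.

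**The concern.** The hypotheses point in one direction and the named tests do not. With two groups, the one-way ANOVA F statistic is the square of the t statistic, so F exceeds its 5% critical value when t is large in either direction, with 2.5% in each tail. Kruskal–Wallis is likewise non-directional. If the 20 per group came from a one-sided calculation, the 90% belongs to a test the trial does not plan to run.

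Two things are at stake. First, the real risk of missing the effect that the protocol calls clinically meaningful would be larger than stated. Second, the criterion for success is not settled. A favourable walking-speed difference with an ANOVA p of 0.08 corresponds to a one-sided p of 0.08/2 = 0.04. That rejects the null as written in the objectives and fails the criterion in the analysis paragraph. Sidedness should not remain open until results are known.

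**Working it through.** **Inputs** (all from Statistical analysis and sample size)

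- Difference in walking speed: 0.2 m/s.
- SD: 0.2 m/s. This is an assumption: ± 0.2 is read as the common SD of the quantity compared. Then d = 0.2/0.2 = 1.
- Alpha 0.05, target power 90%, equal arms of 20.
- Dropout 10%, so completers per group = 20 × 0.9 = 18.

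**Formulas**

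Normal approximation per group: n = 2(z_α + z_β)²/d², where z_α is 1.645 one-sided or 1.960 two-sided, and z_β = 1.282 for 90% power.

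Exact power: noncentral t with 2n − 2 degrees of freedom and noncentrality d√(n/2).

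**Step 1: reproduce the plan's figure, one-sided**

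- Normal approximation: 2(1.645 + 1.282)² = 17.1, so 18.
- Exact t: n = 17 gives 88.6% and n = 18 gives 90.2%, so 18.
- Dropout: 18/0.9 = 20.

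This matches the protocol exactly.

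**Step 2: try the same inputs two-sided**

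- Normal approximation: 2(1.960 + 1.282)² = 21.0 (21.01 unrounded), so 22. Then 22/0.9 = 24.4, so 25 per group.
- Exact t: n = 22 gives 89.97% and n = 23 gives 91.2%, so 23. Then 23/0.9 = 25.6, so 26 per group.

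Neither gives 20.

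**Step 3: power of the planned test at the planned size**

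For 18 completers per group the noncentrality is √(18/2) = 3.0 on 34 degrees of freedom.

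| Completers per group | One-sided 5% | Two-sided 5% (= ANOVA F) |
|---|---|---|
| 18 (10% dropout) | 90.2% | 83.0% |
| 20 (no dropout) | 92.8% | 86.9% |
| 22 | 94.7% | 89.97% |
| 23 | 95.5% | 91.2% |

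The noncentral F with 1 and 34 degrees of freedom also gives 83.0% at 18 per group. The normal approximation is a little more generous: 85.1% at 18 and 88.5% at 20.

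**Step 4: the same shortfall as a detectable effect**

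Two-sided, with 18 per group, 90% power requires d = 1.11, which is 1.11 × 0.2 = 0.22 m/s rather than 0.20 m/s.

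**The case against.** The best defence is that 20 is not a miscalculation. It follows exactly from the protocol's own inputs and its own directional hypotheses. This stands: the fault is a mismatch between the hypotheses and sample size on one side and the named test on the other. It also follows that declaring a one-sided test would be a consistent repair. But the text as it stands names a non-directional test, so one part or the other has to change.

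Second, the one-sided origin is inferred by back-calculation, and ± 0.2 could be the SD of a change rather than of walking speed itself. The inference is strong, because the one-sided route gives exactly 20 and the two-sided route gives 25 or 26. If 0.2 were the SD of the change and changes were compared, d would still be 1 and the figures would be the same.

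Third, 83% describes a single unadjusted walking-speed comparison at one time point, whereas SPPB is also primary and measurements are repeated. That is a fair limit on the figure, and it applies equally to the stated 90%.

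Fourth, the loss is 7 points, power stays above 80%, and type I error is not inflated. An ANOVA p of 0.08 also fails on the plain words of the analysis paragraph. All of this is true and limits the damage. It does not give the trial the power it states, nor bring the stated hypotheses and the stated rejection rule into agreement.

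**Conclusion.** The concern holds. With the stated inputs, 90% power at 20 per group is correct for a one-sided 5% test and incorrect for the ANOVA that the protocol prescribes. The planned test has 83.0% power with 18 completers per group, so the type II error for a 0.2 m/s difference is 17.0% instead of 10%. Even with no dropout, power is 86.9%.

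These figures assume that ± 0.2 is the common SD, that data are normal, that arms are equal and that walking speed is compared once without baseline adjustment. The shortfall is moderate. The unsettled direction of the primary test is the more important reason to correct the text, and the abstract's report that the study had not gone beyond the inclusion phase suggests this can be done before outcome data exist.

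**What to change.** In Primary and secondary objectives, restate H0 as equality of the groups and H1 as a difference. In Statistical analysis and sample size, state that the primary test is two-sided at 0.05, keep 20 per group, and give the power for walking speed as about 83% for the unadjusted comparison with 18 completers per group.

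If the primary analysis is changed to an ANCOVA adjusted for baseline walking speed, power can be restated upwards, with its assumption. The residual SD shrinks by √(1 − r²), where r is the baseline to follow-up correlation. With 18 per group and a two-sided 5% test, power is 91.9% at r = 0.5 but 86.3% at r = 0.3. The protocol gives no value for r, so the assumed value must be stated and justified.

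Two other repairs are consistent. Keeping two-sided 90% power without adjustment needs 26 per group, 52 in total instead of 40. Keeping the directional hypotheses and the 90% means replacing the ANOVA with an explicitly one-sided test and justifying that choice.

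The recommended change costs a few sentences and a less favourable power figure, with no extra participants.

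### The 90% power rests on a ± 0.2 m/s of unstated scale and a walking-speed test with no named baseline adjustment, so it may not hold for the planned ANOVA

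*Protocol article*

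**What the plan says.** Under Statistical analysis and sample size, the protocol gives 20 subjects per group, 90% power and 10% dropout, for an "increase in WS of 0.2 m/s (± 0.2) with an alpha risk of 0.05". It does not say what the ± 0.2 is the SD of, or whether alpha is one- or two-sided.

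Under Primary and secondary objectives, the alternative is directional and worded on walking speed itself: "H1: SPPB score and WS of MFR protocol group > SPPB score and WS of light touch group". No change from baseline appears in it.

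On the test, the protocol says: "Comparison of data between the two groups will be performed with a one-way ANOVA". It adds: "The significance level was set at p ≤ 0.05". No change score and no baseline covariate is named.

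The Intervention section has WS measured on D0 before treatment, so a baseline value exists for everyone. The Discussion looks for the improvement on D21.

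**The concern.** The sample-size sentence speaks of an increase, the hypothesis speaks of WS in each group, and the test is applied to unspecified data. The SD of a change and the SD of a single measurement are different quantities; with equal variances at both times they coincide only when the before-after correlation is 0.5. If the calculation used one and the analysis uses the other, the stated power does not describe the test that will be run. A two-group ANOVA F test is also two-sided, while the hypothesis is directional.

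At stake is the credibility of a negative result. With about 36 evaluable people, an unadjusted comparison of follow-up WS also carries any chance baseline imbalance straight into the estimate, although the value needed to remove it is already collected.

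**Working it through.** **Inputs from the protocol.** Difference 0.2 m/s; ± 0.2 read as an SD; alpha 0.05; power 90%; 20 per group; dropout 10%, so 20 × 0.9 = 18 evaluable per group.

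**Assumed, not in the document.** The correlation r between D0 and follow-up WS, with equal SD at both times. A range is shown.

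**1. Reproducing the 20 per group.** With d = 0.2/0.2 = 1, n per group = 2(z_α + z_β)²/d².
- One-sided: 2(1.645 + 1.282)² = 17.1, so 18; 18/0.9 = 20. This matches.
- Two-sided: 2(1.960 + 1.282)² = 21.0, so 22; 22/0.9 = 24.4, so 25. This does not match.

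The stated figure is therefore correct arithmetic for a one-sided test.

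**2. If 0.2 is the SD of WS and follow-up WS is compared.** Non-central t, 34 df, noncentrality d√(18/2) = 3. Power is 90.2% one-sided and 83.0% two-sided. The gap comes from sidedness alone. An ANOVA of change scores gives the same two figures if 0.2 is the SD of change.

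**3. If 0.2 is the SD of change but follow-up WS is compared unadjusted.** SD of WS = 0.2/√(2(1 − r)), so d = √(2(1 − r)).

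| r | SD of WS | Power two-sided | Power one-sided |
|---|---|---|---|
| 0.3 | 0.169 | 93% | 97% |
| 0.4 | 0.183 | 89% | 94% |
| 0.5 | 0.200 | 83% | 90% |
| 0.6 | 0.224 | 74% | 84% |
| 0.7 | 0.258 | 62% | 74% |
| 0.8 | 0.316 | 45% | 59% |
| 0.9 | 0.447 | 26% | 37% |

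Power drops below 90% once r exceeds about 0.4 two-sided, or about 0.5 one-sided.

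**4. The reverse pairing.** If 0.2 is the SD of WS but change is analysed, SD of change = 0.2√(2(1 − r)). Two-sided power (normal approximation) is 72% at r = 0.3, 85% at 0.5 and 97% at 0.7.

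**5. ANCOVA of follow-up WS on D0 WS.** Residual SD = SD of WS × √(1 − r²), 33 df. Two-sided power:

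| r | 0.2 = SD of change | 0.2 = SD of WS |
|---|---|---|
| 0.3 | 95% | 86% |
| 0.4 | 94% | 89% |
| 0.5 | 92% | 92% |
| 0.7 | 88.5% | 98% |
| 0.8 | 87% | over 99% |
| 0.9 | 85% | over 99% |

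Under both readings, ANCOVA beats the unadjusted follow-up comparison at every r shown.

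**The case against.** The increase can be read as the between-group difference in WS, with 0.2 as the SD of WS. H1 is directional, so one-sided alpha is a natural choice, and 20 per group then reproduces exactly. Equally, a one-way ANOVA can be run on change scores; the protocol says only that data are compared, and an article may leave the analysed variable to a fuller document. Either way, calculation and analysis share a scale. A mismatch requires the change reading for the sample size and the unadjusted-level reading for the test at the same time.

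This stands, and it limits the point. A reader might infer that the ANOVA certainly compares raw levels, that the stated power fails whenever 0.2 is the SD of the increase, or that a true benefit would be missed about half the time. The document supports none of these. The analysed variable is not named. At r = 0.3 power is above 90% even two-sided. The one-in-two figure needs r = 0.8 and an SD of WS of 0.316 m/s, neither of which the protocol gives. Part of the fall in the two-sided figures is also sidedness, not scale; like for like, the one-sided figure at r = 0.7 is 74%.

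What does not go away is that both consistent readings (0.2 as the SD of WS with follow-up WS compared, or as the SD of change with change compared) give 83%, not 90%, for a two-group ANOVA at 0.05.

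**Conclusion.** The point holds in limited form. The protocol fixes an effect, a hypothesis and a test without saying what the 0.2 is the SD of, which WS variable is tested, or whether the test is one-sided. If scale and test agree, the two-sided ANOVA has 83% power with 18 evaluable per arm, and the stated 90% is a one-sided figure. If 0.2 is the SD of change and follow-up WS is compared unadjusted, the stated power may fail, but only for r above about 0.4 two-sided or 0.5 one-sided; at r = 0.7 it would be 62% (74%).

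These results assume equal SDs at both times, 10% dropout and a true difference of 0.2 m/s. It would be too strong to say that the trial is shown to be underpowered, because r and the intended scale are unknown.

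**What to change.** - Make the primary WS analysis an ANCOVA of D21 WS adjusted for pre-treatment D0 WS.
- Word H0/H1 as that baseline-adjusted difference between arms.
- State whether 0.2 m/s is the SD of WS or of its change, and whether the test is one- or two-sided.
- Restate the power on that basis at the planned 20 per group, with the assumed r given.

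The ANCOVA does not restore 90% everywhere: two-sided power is 85–88.5% for r = 0.7–0.9 if 0.2 is the SD of change, and 86–89% for r = 0.3–0.4 if it is the SD of WS. The restated figure should say so. An ANOVA of change would also match a calculation based on the SD of change, but has only 83% two-sided power there.

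The cost is wording in the hypothesis, analysis and sample-size text. No extra participants or measurements are needed.

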#### Randomization and blinding

This study will use a process of allocation concealment which means that recruitment and randomization will be separated. The randomization will take place after the first session of measurements on day 0, just before the interventional part. Patients will be allocated to two groups, a sham group and an experimental group, in sequential order. Opaque envelope, prepared in advance, containing the group assignment, will be drawn by lot by the single therapist. This last will remain blind for the results obtained during evaluation and will be responsible for all the interventions in both groups. Similarly, the evaluator responsible for data collection will be blinded to the treatment allocation group (intervention or sham light touch). The placement of the hands and the timing of the techniques being strictly the same in both cases, the evaluator has no way of knowing which treatment has been applied. Subjects giving their informed consent are informed that a placebo treatment may be administered to them, and that they will not know which treatment has been applied until the end of the study. They are also told that the manipulations received are to be gentle, applied with light pressure and that they will therefore be unable to tell the difference. The subject will be questioned following the last series of measurements on their perception of the protocol received: placebo or experimental.

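### The two-arm comparison is fixed as a one-way ANOVA with redundant post-hoc tests and no stated use of the D0 baseline; a baseline-adjusted model is a free gain in efficiency

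*Protocol article*

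**What the plan says.** All places are in the protocol article.

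- **Statistical analysis and sample size** prescribes the main comparison: "Comparison of data between the two groups will be performed with a one-way ANOVA, followed by a Tukey post-hoc test", with Kruskal–Wallis and Dunn as the alternative. Before that, "Normality will be verified by an Agostino-Pearson test". The only other model named has gender as its second factor: "The gender effect will be considered with a two-way ANOVA, followed by a Bonferroni post-hoc test". No baseline covariate, change score, within-subject factor or group-by-occasion term appears. The same section notes a ceiling effect for SPPB.
- **Design** gives two arms.
- **Intervention** sets the schedule: "The experiment will take place over three measurement times on Day 0 (D0), D7 and D21", and within it "The intervention will be followed by the same measurements as before. This schedule will be reproduced on D7. On D21, only assessment will be done". That is five measurements per person: before and after treatment on D0, before and after on D7, and once on D21.
- **Randomization and blinding** makes the first of these a true baseline: "The randomization will take place after the first session of measurements on day 0, just before the interventional part".
- **Primary outcome** names walking speed (WS) and SPPB. The analysis text ties neither to an occasion; only the Discussion points to D21, as a hope.

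**The concern.** The named method does not match the design. A one-way ANOVA on two groups gives the same result as a two-sample t-test, so a Tukey or Dunn step adds nothing. Those steps would have work to do only if the group-by-occasion cells (2 × 5 = 10) were entered as separate groups, and a one-way ANOVA cannot properly handle five measurements of the same person.

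The D0 value measured before randomization is usually the best predictor of the later value, and it costs nothing more to use. In a trial of 40 people, leaving it out of the model can cost a useful amount of power.

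A normality test on about 18 people per arm is also a weak basis for choosing the method. It could lead to different methods for the same outcome on different days. For SPPB the departure from normality is foreseeable from the ceiling effect the protocol itself mentions, so nothing is gained by waiting for the data.

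**Working it through.** **Inputs from the protocol article:** difference 0.2 m/s, ± 0.2, alpha 0.05, power 90%, 20 per group, 10% dropout. Completers per arm: 20 × 0.9 = 18. **Assumption:** r, the correlation between the D0 and later WS values. It is not given, so a range is shown.

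**1. The plan's own figure.** n per arm = 2 (z₁ + z₂)² (SD/difference)², with SD/difference = 0.2/0.2 = 1.
- One-sided 5%: 2 × (1.645 + 1.282)² = 17.1, so 18; 18/0.9 = 20. This matches.
- Two-sided 5%: 2 × (1.960 + 1.282)² = 21.01, so 22; 22/0.9 = 24.4, so 25. No match.

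The 20 per group is therefore a one-sided, two-sample comparison at a single occasion (or of a single change score), without covariate adjustment.

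**2. The stated test at 18 per arm.** Noncentrality = (0.2/0.2) × √(18/2) = 3, on 34 degrees of freedom. Two-sided power is 83%, and one-sided power is 90%. The Tukey critical value for two groups, put on the t scale, is 2.03, the same as the t-test's, so the post-hoc step changes nothing.

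**3. ANCOVA if 0.2 is the SD at one occasion.** Residual SD = 0.2 √(1 − r²); noncentrality = 3/√(1 − r²); 33 degrees of freedom; two-sided 5%.

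| r | Residual SD | Unadjusted power | ANCOVA power |
|---|---|---|---|
| 0 | 0.200 | 83% | 83% |
| 0.3 | 0.191 | 83% | 86% |
| 0.5 | 0.173 | 83% | 92% |
| 0.6 | 0.160 | 83% | 95% |
| 0.7 | 0.143 | 83% | 98% |

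**4. ANCOVA if 0.2 is the SD of the change from D0.** The SD at one occasion is then 0.2/√(2(1 − r)). The ANCOVA residual SD is that times √(1 − r²), which simplifies to 0.2 √((1 + r)/2).

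| r | Residual SD | Change-score ANOVA power | ANCOVA power |
|---|---|---|---|
| 0.3 | 0.161 | 83% | 95% |
| 0.5 | 0.173 | 83% | 92% |
| 0.6 | 0.179 | 83% | 90% |
| 0.7 | 0.184 | 83% | 88% |

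The two readings move in opposite directions with r. ANCOVA is ahead under both for r from 0.3 to 0.7.

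**The case against.** The main counter-argument is that an unadjusted comparison of two randomized arms at one occasion is unbiased and keeps its type I error, and that chance baseline imbalance is already reflected in its standard error. That stands: adjustment here buys precision and does not repair a bias. With two groups the Tukey step is redundant but harmless.

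Three further limits also stand.
- The text does not define which data enter the ANOVA. The sample-size sentence speaks of an increase in WS, so an analysis of change from D0 is not excluded, and that would use the baseline. The document does not say that baseline is ignored; it does not state how, or whether, it is used.
- The gain depends on a correlation that the document does not give. With 0.2 as the SD at one occasion, it is nil at r = 0 and 3 points at r = 0.3.
- The gap between 83% and the planned 90% comes from sidedness: the sizing reproduces one-sided, while the ANOVA F test is non-directional. It should not be attributed to the missing covariate.

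A reader might infer from the post-hoc tests that all ten group-by-occasion cells will be entered as independent groups. Tukey over ten cells would take power for the D21 between-arm contrast to about 42%. The wording speaks of two groups, however, and nowhere mentions ten cells. That loss would also come from the multiplicity penalty. Treating repeated values as independent distorts the standard error of a within-person change, but at a single occasion the two arms are different people.

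**Conclusion.** The point holds as a free improvement and should be fixed. The protocol commits to a method whose post-hoc step is redundant for two arms, states no use of a baseline that it collects before randomization, and lets a normality test choose the method.

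On the plain two-group reading, adjusting for D0 raises two-sided power from 83% to between 86% and 98% for r of 0.3 to 0.7. On the change-score reading it raises it from 83% to between 95% and 88% over the same range. These figures assume 18 completers per arm, a difference of 0.2 m/s, the stated ± 0.2 read as an SD, and correlations that are assumed.

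The document does not support the stronger conclusion that the primary test is invalid or biased. That would need the ten-cell reading or a pooling of all five values per person, and the text states neither.

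**What to change.** Replace the ANOVA, Tukey, Kruskal–Wallis and Dunn sequence in the statistical section.

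- **WS, primary analysis:** ANCOVA of WS at D21 with group as factor and the D0 pre-treatment WS as covariate. Report the adjusted between-group difference with its 95% CI. D21 is the occasion to which the Discussion points; the sponsor should confirm it as primary. Only the first D0 session can serve as baseline, because the D7 pre-treatment value follows the first intervention.
- **WS, supportive analysis:** a mixed model over the post-baseline occasions with baseline, group, occasion and group × occasion, and a within-person correlation.
- **SPPB:** one pre-specified rank-based analysis adjusted for D0 SPPB, for example a rank analysis of covariance.
- **Normality test:** drop it as the selector of the method. For WS, inspect residual plots and give a rank-based sensitivity analysis.

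The cost is wording. The baseline is already collected, and no extra visits or participants are needed. The mixed model may need a free package alongside the named software.
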